### Sample size

This study adopts a three-arm design to evaluate the eHealth intervention’s superiority to usual care and non-inferiority to face-to-face intervention using a hierarchical testing procedure.^63^ The trial will be termed successful if superiority of the eHealth intervention to usual care as well as non-inferiority of the eHealth intervention to the face-to-face intervention has been shown. A hierarchical testing procedure will be applied, first testing superiority, followed by testing non-inferiority if and only if superiority was shown. Consequently, no correction for multiple testing needs to be applied. Note that if superiority was shown, but showing non-inferiority failed, it is still allowed to conclude that eHealth intervention is effective, but not that it can replace the face-to-face intervention.

The primary outcome used to test superiority as well as non-inferiority is the PDI measured at 6 months. Both tests will be based on the comparison of the mean value after correction for the baseline PDI (Analysis of Covariance (ANCOVA) approach). The assumed SD of the PDI and the correlation between baseline and 6 months equal 15 and 0.65, respectively, and were obtained from pilot data on 28 subjects.^45^ No difference in PDI was expected between face-to-face and eHealth self-management and the region of non-inferiority was defined as a difference of five PDI points. The sample size was calculated to have at least 80% power to show non-inferiority based on a one-sided test with alpha equal to 0.025 (hence, equivalent to a two-sided test with alpha=0.05). A simulation study with 2000 simulations was used, and the power was defined as the percentage of sampled datasets where non-inferiority has been shown using the ANCOVA approach. With 79 subjects in the eHealth and the face-to-face group, there is at least 80% power to show non-inferiority.

To show superiority of eHealth intervention vs usual care based on a two-sided (ANCOVA) test with alpha equal to 0.05, 83 subjects per group are required to detect with at least 80% power a difference of 5 points. Note that having at least 80% power for each of the two comparisons separately does not guarantee 80% power simultaneously.

Strictly speaking, fewer patients are required in the face-to-face group compared with the two other groups. However, given the small difference (79 vs 83), it was decided to recruit an equal number of patients in each of the three groups.

Based on the number of subjects required for the primary outcome, more than 80% power is also guaranteed for the key-secondary outcome Survey of Pain Attitudes (SOPA). Indeed, to detect a difference in SOPA of 4 points, assuming an SD of 7.5 and a correlation between baseline and 6 months of 0.30, 52 subjects per group are required. Further, 50 subjects per group are required to show with at least 80% power non-inferiority of eHealth intervention, setting the margin of non-inferiority equal to 4 points. Assumptions for the key secondary outcome measure are based on the pilot study of Moseley *et al* on PSE in a non-cancer population.^64^

To anticipate a dropout percentage of 7%, the sample size in each group will be increased with factor 100/93=1.075, yielding 90 subjects per group, hence 270 subjects in total.

### Data analysis

A constrained longitudinal data analysis model (cLDA) will be used to compare the PDI between the three groups.^65^ In the cLDA, both the baseline and post-baseline values (12 weeks, 6 months and 12 months) are modelled as dependent variables, as opposed to a (longitudinal) ANCOVA model in which the baseline value is included as a covariate. Although the baseline measure is included in the response vector in cLDA, the true baseline means are constrained to be the same for different treatment groups due to randomisation, and this analysis provides an adjustment for the observed baseline difference in estimating the treatment effects. As opposed to the ANCOVA model, the cLDA approach can handle the presence of missing data and produces unbiased estimates if the missing data mechanism is missing at random. Additionally, 95% CIs for the group-specific mean post-baseline values will be constructed as well as the confidence intervals for the differences between the groups. The stratification variable will be added as a fixed factor in the model.

The primary analysis refers to the comparison after 6 months. A hierarchical testing procedure will be applied for the two primary comparisons. First, the difference between the eHealth intervention and usual care will be tested based on a two-sided test with alpha set at 0.05. If significant, non-inferiority of the eHealth intervention vs the face-to-face intervention will be tested based on a one-sided non-inferiority test with alpha set at 0.025 and defining the margin of non-inferiority as a difference of 5 PDI points. For the superiority comparison, the analysis will be based on the intention-to-treat principle, that is, all randomised patients will be analysed in the allocated group. However, for the non-inferiority comparison, the analysis will be based on the as-treated analysis set.

For the continuous secondary outcomes, the same cLDA model as for the primary outcome will be used. For the key-secondary outcome SOPA, a non-inferiority test (eHealth vs face-to-face intervention) will be performed defining the margin of non-inferiority as a difference of 4 points (one-sided test with alpha equal to 0.025). Note that for the other secondary outcomes, no inferiority tests will be performed, but all differences between groups will be evaluated using two-sided 95% CIs. The alpha-level for the secondary outcomes is set at 0.05, without a priori planned corrections for multiple testing. Thus, only for the key-secondary outcome SOPA a strong claim is possible without correction for multiple testing. Data analysis will be performed by The Leuven Biostatistics and Statistical Bioinformatics Centre of KU Leuven, who is blinded to group allocation.

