### Trial design and study setting

The trial is a parallel, three-arm pragmatic randomised study, approved by the Ethics Committees of the University Hospitals Leuven and Antwerp (BUN B3002023000132) on 30 January 2024. The first participant was enrolled on 26 May 2024. Recruitment is expected to continue until January 2028, resulting in the primary completion in June 2028. Given a 1-year follow-up, the anticipated study completion date is January 2029. A schedule of the trial is presented in table 1.

**Table 1 T1:** Schedule of enrolment, interventions and assessments of the PECAN trial

Timepoint	Study period							
	Enrolment		Allocation	Post-allocation				
	-t_2_ Referral	-t_1_ telephone consult	0	t_1_ baseline	t_2_ 6 weeks after baseline	t_3_ 12 weeks after baseline	t_4_ 6 Mo after baseline	t_5_ 12 Mo after baseline
Enrolment								
Eligibility screen	X							
Informed consent		X						
Randomisation			X					
Allocation			X					
Interventions								
				Education	PA coaching			
eHealth intervention			n=90	x	x			
Face-to-face intervention			n=90	x	x			
Usual care			n=90					
Assessments								
Pain-related disability (primary outcome)*				X		X	X†	X
Pain-related outcomes, including pain beliefs and attitudes (key secondary outcome)*				X	(X)†	X	X	X
Physical outcomes*				X		X	X	X
Psychosocial outcomes*				X		X	X	X
Health economic outcomes*							X	X

* See online supplemental appendix C for details on the content of the different assessments at each point in time.

† Primary endpoint of the trial.

† The key secondary outcome ‘pain beliefs and attitudes’ is the only outcome collected at 6 weeks.

PA, physical activity; PECAN, Pain Education and Coaching of Activity Needs in breast cancer survivors.

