### Participant screening, recruitment and consent

Participants experiencing persistent pain after breast cancer treatment are recruited in the University Hospitals of Leuven and Antwerp, as well as from general practitioners’ practices in Flanders and through self-referral. Following referral, an initial screening is conducted by a member of the research team. Eligible participants receive a detailed explanation of the study over the phone, along with an information sheet sent via email. Participants are not blind to the intervention nor the different arms. If needed, a second phone consultation is provided before obtaining informed consent. The consent form can be signed either digitally (via email) or on paper (via postal mail). An example of the informed consent form can be found in online supplemental appendix A.

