### Outcomes

Assessments will be performed at baseline, after 6 weeks, 12 weeks and 6 and 12 months after baseline. However, because of feasibility limitations and relevance, not all outcome parameters are assessed at each assessment time point. Online supplemental appendix C presents a table with the study outcome measures by assessment time point. Study data will be collected and managed using Research Electronic Data Capture (REDCap) electronic data capture tools hosted at Antwerp University. REDCap is a secure, web-based software platform designed to support data capture for research studies.^53 54^

The primary outcome (primary objective) is pain-related functioning at 6 months post-baseline, assessed using the Pain Disability Index (PDI).^55^ The reliability of the Dutch version is good in the breast cancer population.^56^

As a secondary objective, this research project will determine the effect of the educational part alone of the eHealth self-management programme on pain beliefs and attitudes (key secondary outcome) at 6 weeks (ie, before the start of PA coaching). To determine other *secondary outcomes*, we formulated a programme theory delineating how intervention components, mechanisms and contextual factors of the eHealth programme contribute to intermediate, short-term and long-term results. Employing HAPA as our theoretical framework, we initiated the process by identifying the targeted behaviour (eg, an active lifestyle) and primary outcome (eg, pain-related disability). Subsequently, we identified the necessary steps in the programme and listed the used behaviour change techniques in each of these steps. We also considered contextual factors and possible factors that might hinder or facilitate (moderators) the hypothesised causal chain of mechanisms of change (mediators). Three sessions with health psychologists, physical therapists and behaviour change experts to ensure a thorough development of our programme theory. A mapping of the items of self-reported measures onto constructs relevant to the intervention took place. This allowed us to refine available items, develop new items that were relevant but missing and drop (subscales of) self-reported measures that proved irrelevant according to our programme theory. This approach ensured a comprehensive assessment of patient-related, pain-related, physical and psychosocial outcomes of our programme theory components and outcomes.

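### Table 1 places the self-reported baseline PDI after allocation in an open-label trial, so the equal-baseline assumption behind the primary contrast is not assured by randomisation

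*Protocol article*

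**What the plan says.** Table 1 (Trial design and study setting) puts randomisation and allocation at time 0. The block that follows is headed "Post-allocation", and its first column is the t1 baseline. The first PDI mark is in that column, where the education component also begins. No outcome is marked in any earlier column.

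The section on screening, recruitment and consent states: "Participants are not blind to the intervention nor the different arms".

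The Data analysis section models baseline and follow-up PDI jointly in a constrained longitudinal model (cLDA). It justifies the constraint by saying that "the true baseline means are constrained to be the same for different treatment groups due to randomisation", and adds that "this analysis provides an adjustment for the observed baseline difference in estimating the treatment effects". The other continuous outcomes use the same model.

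The article does not say whether the baseline questionnaire is completed before the participant is told her arm. Ethical considerations places only consent before data collection.

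**The concern.** The PDI is the participant's own rating of disability. Someone who has just learned that she will get a mailed brochure, rather than a chatbot or a therapist, may answer differently from how she would have answered an hour earlier. Randomisation gives equal expected baselines only for answers that such knowledge cannot influence. If the schedule is followed as printed and the arm is known at t1, that guarantee is lost.

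The model would then treat a shift caused by allocation as chance imbalance and carry it into the 6-month contrast. At stake is the superiority test against usual care, which comes first in the hierarchy and decides whether non-inferiority is tested at all.

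**Working it through.** **Inputs from the article (Sample size).** "The assumed SD of the PDI and the correlation between baseline and 6 months equal 15 and 0.65, respectively". For superiority, at two-sided alpha 0.05, "83 subjects per group are required to detect with at least 80% power a difference of 5 points". For the comparison with face-to-face care, "the region of non-inferiority was defined as a difference of five PDI points".

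**Input assumed.** The between-arm shift d in reported baseline PDI caused by knowing the arm. The article gives no figure; 1 and 2 points are used for illustration.

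**Step 1: reproduce the plan's figure.**
- Residual SD after baseline adjustment: 15 × √(1 − 0.65²) = 11.40.
- Normal approximation: n = 2 × [11.40 × (1.960 + 0.842) / 5]² = 81.6, so 82 per group. With the noncentral t, 83 is the first n to reach 80% (80.2%). The plan's 83 is reproduced, and 83 / 0.93 rounds up to its 90.
- Standard error of the adjusted contrast at 83 per group: 11.40 × √(2/83) = 1.77.

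**Step 2: bias.** With complete baseline and 6-month data, the cLDA contrast equals the ANCOVA contrast: the raw 6-month difference minus slope × the observed baseline difference. With equal SDs the slope is the correlation, 0.65. A baseline difference d that knowledge of the arm creates, and that is absent at 6 months, moves the contrast by 0.65 × d in magnitude.
- d = 1: 0.65 points.
- d = 2: 1.30 points, or 1.30 / 5 = 26% of the 5-point target difference.

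**Step 3: direction.** Taking a higher PDI as more disability, a usual-care group that reports a worse baseline after learning its arm works against eHealth; one that reports a better baseline works in its favour. The article does not settle which.

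**Step 4: error rates for superiority** (normal approximation, b = bias).
- Two-sided type I error = Φ(−1.96 + b/1.77) + Φ(−1.96 − b/1.77).
- Power for a true 5-point benefit when the bias is against eHealth = Φ((5 − b)/1.77 − 1.96).

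| d (assumed) | b | Type I error | Power, bias against eHealth |
|---|---|---|---|
| 0 | 0 | 5.0% | 80.7% |
| 1 | 0.65 | 6.6% | 69% |
| 2 | 1.30 | 11.4% | 55% |

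A false claim for eHealth and a loss of power need opposite signs of bias, so those two consequences are alternatives.

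**Step 5: simulation.** Three arms of 83, no true effect, usual-care baseline shifted down by 2 points, 10,000 runs. The mean adjusted contrast was −1.31 (expected −1.30) and the rejection rate 11.5%. The raw 6-month difference stayed at about 0.

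**Step 6: carry-over.** If a fraction c of the shift is still present in the 6-month answers, the adjusted contrast carries (c − 0.65) × d and the unadjusted one c × d. The figures above are for c = 0. At c = 0.65 the adjusted bias vanishes. Above c = 0.325 the adjusted contrast is the less biased of the two.

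**The case against.** The strongest reply is that disclosure before baseline is inferred. Table 1 shows allocation listed before t1, not that the participant has been told. Allocation and randomisation describes an independent person working in a restricted file and is silent on when participants are informed. The blinding sentence sits in the consent section and does not say that they know their own arm at t1. The table is also schematic: its columns double as the periods that start there. This stands, and the bias is therefore possible, not shown. One detail leans the other way. The study identifier is assigned at the allocation step, and a trial number appears on all participant communication. If these are the same number, a baseline form carrying it would follow allocation, though not necessarily disclosure.

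A second reply is that a condensed article may leave such operational detail to the full protocol. That would answer a complaint about silence. Here the printed schedule and the printed justification of the model do not fit together, and that can be raised from the article itself.

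Three stronger readings are tempting and not supported:
- That cLDA is the wrong model. ANCOVA on the same baseline has the same bias, and the constraint is sound if baseline precedes disclosure.
- That both primary contrasts are equally exposed. The two active arms share the same two parts and the same education content, so there is less reason to expect a baseline shift between them than between eHealth and a brochure.
- That the bias could never be detected or removed. A comparison of 6-month means without baseline avoids it when the shift does not persist, at a cost in precision.

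**Conclusion.** The point holds in conditional form. As printed, the schedule does not support the reason given for constraining the baseline means. If participants know their arm when they complete the baseline PDI, and this shifts their answers without lasting to 6 months, the adjusted contrast is off by about 0.65 points per point of shift, in an unknown direction. The size of the shift and the absence of carry-over are assumptions; the slope and standard error come from the plan's own inputs. The concern is strongest for eHealth versus usual care. It deserves action because recruitment is expected to run until January 2028 and the remedy is cheap.

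**What to change.** 1. Complete and lock the baseline REDCap questionnaires before allocation is disclosed to the participant, preferably before it is made. State this order in the text and move t1 ahead of allocation in Table 1. If practice already follows it, correct the table only.
2. For participants already enrolled, compare the date of baseline completion with the date of disclosure and flag those in the other order.
3. If there are any, add a sensitivity analysis comparing 6-month PDI means without the baseline constraint or adjustment. It should not compare changes from baseline, which would carry the shift with a slope of 1 instead of 0.65.

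The cost is a reordered online form, a table correction and one extra analysis, with no added participants and no change to the primary model. The sensitivity analysis is less precise: its SE at 83 per group is 15 × √(2/83) = 2.33 against 1.77, and power for 5 points is Φ(5/2.33 − 1.96), about 57%. It should therefore be read beside the primary result, with step 6 in mind, and not in place of it. That loss is the reason to secure the order now.

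### The confirmatory non-inferiority test rests on an as-treated set alone, so the conclusion that eHealth can replace face-to-face is not protected by randomisation

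*Protocol article*

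**What the plan says.** The Data analysis section of the protocol article assigns a different analysis set to each of the two primary comparisons.

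- Superiority over usual care: "For the superiority comparison, the analysis will be based on the intention-to-treat principle, that is, all randomised patients will be analysed in the allocated group".
- Non-inferiority to face-to-face: "However, for the non-inferiority comparison, the analysis will be based on the as-treated analysis set". The article neither defines this set nor names a second one for this comparison.

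Both comparisons use the constrained longitudinal model (cLDA), in which "the true baseline means are constrained to be the same for different treatment groups due to randomisation". Non-inferiority is judged with a "one-sided non-inferiority test with alpha set at 0.025" and a margin of 5 PDI points.

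The Sample size section shows what depends on the result. "The trial will be termed successful if superiority of the eHealth intervention to usual care as well as non-inferiority" to face-to-face have both been shown. If superiority is shown but non-inferiority is not, "it is still allowed to conclude that eHealth intervention is effective, but not that it can replace the face-to-face intervention".

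**The concern.** In its usual meaning, an as-treated set groups people by the treatment they took up, not by the arm they were randomised to. Someone allocated to the chatbot who never starts it is dropped or counted elsewhere. Uptake is partly the participant's choice. The trial is unblinded, the eHealth programme is self-paced and stand-alone, and the face-to-face programme asks for nine visits in 12 weeks. People who disengage may differ in prognosis from those who stay, and adjusting for baseline PDI removes only the part of that difference that baseline PDI carries.

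The article therefore bases one of its two confirmatory tests on a comparison that randomisation does not protect. The statement that no multiplicity correction is needed also assumes that each step of the hierarchy holds its own error level. What is at stake is the claim that eHealth can replace face-to-face, and with it the definition of a successful trial.

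**Working it through.** **Inputs from the Sample size and Data analysis sections.** SD 15 and baseline to 6-month correlation 0.65; margin 5; one-sided alpha 0.025; assumed true difference 0; 79 per group for non-inferiority and 83 for superiority; 7% dropout; 90 recruited per group.

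**1. The plan's own figures.**
- Residual SD after baseline adjustment = 15 × √(1 − 0.65²) = 11.40.
- n per group = 2 × [11.40 × (1.960 + 0.842) / 5]² = 81.6, so 82. This serves both tests, since each has a distance of 5 and the same alpha.
- Superiority: 83 is stated, which agrees. Dropout: 83 / 0.93 = 89.2, so 90, which agrees.
- Non-inferiority: 79 is stated against 82. Power at 79 is 78.7% by the normal formula. The Monte Carlo error of the plan's 2000 simulations (standard error 0.9 percentage points) could explain the gap, and the present point does not turn on it.

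**2. Error at the margin if the as-treated comparison is shifted.**
- Standard error of the adjusted difference with 83 per group = 11.40 × √(2/83) = 1.77.
- Let s be the net shift in favour of eHealth caused by forming groups on treatment received. With a true difference of 5, the chance of declaring non-inferiority is 1 − Φ(1.96 − s/1.77).

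| s (PDI points) | One-sided error |
|---|---|
| +1.0 | 8.2% |
| +0.5 | 4.7% |
| 0 | 2.5% |
| −0.5 | about 1.3% |
| −1.0 | about 0.6% |

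The article gives no value for s. As an illustration, if 10% of the eHealth arm never start, are 5 to 10 points worse at 6 months after adjustment, and are removed, then s = 0.10 × 5 to 0.10 × 10 = +0.5 to +1.0. The same pattern in face-to-face only reverses the sign. Equal departures in both arms with equal gaps give s = 0.

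**3. Simulation (4,000 runs, 84 per arm, true full-adherence difference 5).** All settings are assumptions: departures occur in the eHealth arm only and, in the first two rows, correlate 0.3 with unobserved prognosis.

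| Handling in the as-treated set | 10% depart | 20% | 30% |
|---|---|---|---|
| Dropped | 5.6% | 9.6% | 13.9% |
| Regrouped to face-to-face | 9.5% | 20.3% | 28.8% |
| No link to unobserved prognosis | 2.1% to 2.7% throughout | | |

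**4. Is the baseline constraint a separate source of bias?** When departures also depend on baseline (correlation 0.3), the as-treated groups differ at baseline by about −0.9 to −3.5 PDI points, so equal baseline means no longer hold. With 20% regrouped and a true difference of 5, the estimates were:
- selection on baseline only: cLDA 4.95, ANCOVA 4.95;
- selection also on unobserved prognosis: cLDA 3.17, ANCOVA 3.17.

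The two models agree in both cases. The bias in the second comes from the loss of comparable groups, not from the constraint.

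**5. Would ITT alone be enough?** When eHealth participants switch to face-to-face, the allocated groups become more alike. With 10%, 20% and 30% switching and a full-adherence difference of 5, the allocated-group test declared non-inferiority in about 5%, 9% and 13% of runs.

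**The case against.** The strongest defence is that a treatment-received set answers a real problem. Step 5 shows that ITT can favour a non-inferiority claim when people switch. This stands, and it is why the fault lies in relying on the as-treated set alone, not in using a second set. It does not justify making a non-randomised comparison the only basis.

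A second objection is that inflation is not established. This also stands. The article gives no departure rate, and it names visit burden, mobility and time constraints as barriers to face-to-face care, so departures could be as common there. It does not say that eHealth participants can enter the face-to-face programme, which is delivered by therapists recruited and trained for the study. A reader might infer that the plan makes a false non-inferiority claim more likely. The documents show only that the error is not controlled; it could move either way.

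Third, the 4.7% to 8.2% illustration removes people and re-labels nobody, so a per-protocol set is open to the same shift. That is true, and it is why neither set should stand alone.

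A reader might also infer that the equal-baseline constraint makes the model wrong and so biases the test. In an as-treated set the constraint does lose the justification the article gives for it, but step 4 shows that it adds no bias of its own to the 6-month difference. Entering baseline PDI as a covariate instead would return the same estimate.

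Finally, the article is condensed, and an analysis plan that is not shown may add an ITT analysis or define the set. That possibility does not change what the article fixes as the basis of the confirmatory test.

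**Conclusion.** The point holds in this form: the confirmatory non-inferiority test should not rest on an as-treated set alone. The choice is stated in the article, and both trial success and the replacement conclusion depend on it.

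The size is conditional. It needs departures from allocation that are linked to prognosis beyond baseline PDI and that do not cancel between arms. Net shifts from −1.0 to +1.0 PDI points move the error at the margin between about 0.6% and 8.2%, against a nominal 2.5%. With no departures the as-treated and allocated groups coincide and nothing changes.

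The conclusion that eHealth is effective against usual care is not affected, because that comparison is made by ITT and is tested first.

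**What to change.** Amend the Data analysis section, and the analysis plan to match, so that:

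- non-inferiority is tested in all randomised participants as allocated (ITT), and also in a per-protocol set defined before the data are analysed, which excludes major departures and never moves anyone to another arm;
- non-inferiority is claimed only if both analyses meet the 5-point margin;
- as-treated is kept as a labelled sensitivity analysis, without citing randomisation as the reason for equal baseline means.

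For the difference between allocated groups, the joint rule cannot have a higher error than the ITT test. For the full-adherence difference it cannot exceed the smaller of the two errors, which under switching may still be above 2.5%. Departures should therefore be reported by arm.

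The cost is revised wording and one extra model run, with no extra patients or data. At a true difference of 0, the ITT test with 83 evaluable per group has 80.7% power, which 90 recruited with 7% dropout supplies. Requiring both sets to agree loses some power, since joint power cannot exceed that of the smaller set: about 77% if 10% of 84 per arm are excluded, and about 72% if 20% are. An as-treated set that drops the same people would lose as much.

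### The SOPA non-inferiority claim is not conditional on eHealth first beating usual care on SOPA, so on its own it cannot separate two programmes that work from two that do not

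*Protocol article*

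**What the plan says.** For the PDI, the Sample size and Data analysis sections set a fixed order for the two primary comparisons. eHealth is first compared with usual care (two-sided 0.05). Then: "If significant, non-inferiority of the eHealth intervention vs the face-to-face intervention will be tested".

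For SOPA, the Data analysis section applies the same longitudinal model to the continuous secondary outcomes and names one formal test: "a non-inferiority test (eHealth vs face-to-face intervention) will be performed defining the margin of non-inferiority as a difference of 4 points", as a "one-sided test with alpha equal to 0.025". No preceding step is stated. The section adds that, among the secondary outcomes, SOPA alone can support a strong conclusion with no multiplicity correction.

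The Sample size section plans two SOPA comparisons. One is "to detect a difference in SOPA of 4 points, assuming an SD of 7.5 and a correlation between baseline and 6 months of 0.30", requiring 52 per group. The other is non-inferiority with a 4-point margin, requiring 50 per group. The SOPA assumptions are attributed to a pilot study of pain science education in a non-cancer population.

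The Outcomes section gives the purpose: "this research project will determine the effect of the educational part alone of the eHealth self-management programme on pain beliefs and attitudes", at 6 weeks, before activity coaching starts.

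**The concern.** Non-inferiority to an active comparator is informative about benefit only if that comparator works on the same scale, in the same population and at the same time. The trial has a usual-care arm that can show this, and the plan uses it in that way for the PDI. The PDI margin (5 points) also equals the difference sought against usual care (5 points), but there the superiority step protects the claim. SOPA has the same margin structure without the step.

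A margin of 4 points against a sought difference of 4 points preserves none of that difference. Non-inferiority can therefore be met when neither programme changes beliefs, or when face-to-face helps a little and eHealth not at all. The stated aim, the effect of the education alone, is answered by the contrast with usual care. At stake is what a statement of non-inferiority on pain beliefs would mean. PDI superiority at 6 months does not supply the missing evidence, because by then the effect combines education and activity coaching.

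**Working it through.** **Inputs.** From the Sample size section: SOPA SD 7.5, baseline correlation 0.30, difference sought 4, margin 4, 83 evaluable per group (the PDI superiority requirement), 90 randomised per group after allowing for 7% dropout. From the Data analysis section: one-sided 0.025 for non-inferiority. The correlation is stated for baseline to 6 months, whereas the SOPA endpoint is at 6 weeks; I use it as given and vary it below.

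**Step 1: reproduce the plan's sample sizes.** Residual SD after baseline adjustment = 7.5 × √(1 − 0.30²) = 7.155. With a normal approximation, n per group = 2 × (1.960 + 0.842)² × 7.155² / 4² = 50.2, so 51 for either comparison (non-inferiority taken at a true difference of zero). The plan states 52 and 50. A noncentral-t calculation gives 52 for superiority (80.6% power) and 79.0% power for non-inferiority at 50. The plan's figures are reproduced to within two patients.

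**Step 2: margin against the difference sought.** 4 / 4 = 100%.

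**Step 3: chance of meeting the test as written.** SE of the difference at 83 per group = 7.155 × √(2/83) = 1.11. If face-to-face is truly better than eHealth by δ points, P(non-inferiority) = Φ((4 − δ)/1.11 − 1.96).

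**Step 4: the same with superiority over usual care on SOPA required first.** The two contrasts share the eHealth arm, so their correlation is 0.5. The joint probability is bivariate normal, with eHealth no better than usual care.

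| True gain over usual care (eHealth / face-to-face) | Non-inferiority as written, 83 per arm | As written, 90 per arm | Superiority and non-inferiority, 83 per arm |
|---|---|---|---|
| 0 / 0 | 95.0% | 96.3% | 2.5% |
| 0 / 1 | 77.1% | 80.3% | 2.5% |
| 0 / 2 | 43.7% | 46.6% | 2.2% |
| 0 / 3 | 14.5% | 15.3% | 1.4% |
| 4 / 4 | 95.0% | 96.3% | about 90% |

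The first and last rows are identical as written (95.0%) and far apart once the superiority step is added. A three-arm ANCOVA simulation (4,000 runs per scenario) agrees. At 83 per arm with no effect anywhere, it gives 95.1% for non-inferiority and 2.8% for both steps. With 4 points for both programmes, both steps are passed in 90.1% of runs at 83 per arm and 93.2% at 90 (the normal approximation gives 91.2% and 93.5%).

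**Step 5: sensitivity to the correlation.** With no baseline adjustment (SD 7.5), the chance of meeting non-inferiority at zero difference is 92.7% at 83 per arm and 94.5% at 90. The result does not depend on the correlation.

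**The case against.** The strongest reply is that the usual-care contrast on SOPA is already planned. The Sample size section powers a comparison "to detect a difference in SOPA of 4 points" alongside non-inferiority. The Data analysis section fits the three-arm model to SOPA with confidence intervals for between-group differences. The assessment schedule excludes no arm at 6 weeks. An ineffective education module would therefore show in the SOPA data themselves, with about 95% power for a 4-point effect at 83 per arm. This stands: the comparison is present, and what is absent is the rule linking it to the non-inferiority claim.

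Second, the 95% is simply the power of this test at equality. It would be the same if both programmes gained 10 points, so it does not measure how poor the margin is. This also stands. The 77%, 44% and 14% figures show better what the margin lets through.

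Third, a reader might infer that the authors intend to present SOPA non-inferiority by itself as proof that the education works, or that an ineffective module would go unnoticed at 6 weeks. The article supports neither. It says that a strong conclusion on SOPA is possible, not that it rests on non-inferiority alone.

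Fourth, trial success is defined on the PDI only, and a full protocol or analysis plan that is not shown may set the SOPA order. That limits the weight of the point. It does not remove it, because the article states the order for the PDI, states the SOPA test without one, and attaches a strong conclusion to that outcome.

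**Conclusion.** The point holds in a limited form. The SOPA non-inferiority test is fixed with a margin equal to the whole difference sought and without the superiority condition that protects the PDI. Taken alone, it cannot tell apart two effective programmes and two ineffective ones: about 95% of trials meet it in either case at 83 per arm. It also passes 44% of the time if face-to-face gains 2 points and eHealth none.

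It does not follow that the usual-care contrast is missing or underpowered, or that a misleading claim is likely; the contrast will be estimated and reported.

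The figures rest on the plan's SD and correlation, normally distributed estimates, and 83 to 90 analysed per arm. The matter affects how the key secondary claim is read, not the primary result. It is worth correcting because the correction is cheap.

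**What to change.** In the Data analysis section, state that SOPA at 6 weeks is tested in the PDI order: first eHealth against usual care (two-sided 0.05), then non-inferiority to face-to-face (one-sided 0.025, 4-point margin) only if the first is significant in favour of eHealth. Report face-to-face against usual care, with its confidence interval, beside it. State that non-inferiority on SOPA without superiority over usual care will not be read as evidence that the eHealth education works. The fixed order also means that no correction is needed between these two SOPA tests.

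The cost is wording only, with no new data or participants. Recruitment is expected to run until January 2028, so the change can be made before results are known. If both programmes truly gain 4 points, the chance of the SOPA non-inferiority claim falls from about 95% to about 90% at 83 per arm (from about 96% to 93% at 90).

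Tightening the margin instead would be expensive. A 2-point margin needs 2 × (1.960 + 0.842)² × 7.155² / 2² = 201 per group, and has only about 43% power at 83. Adding the superiority condition is the practical remedy.
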